a. The balance plate is arranged on the platform; the height of the foot platform is adjusted; feet are in contact with the ground; and curtsying subjects sit at 90–100 degrees.b. Adjust the seat of the subject and position the femur large rotor on the balance plate A3–A5 axis.c. Adjustment of the feet to shoulder width of subjectd. Chest rise, eyes to the fronte. Subject with arms crossed, elbow, shoulder proneness of 45 degrees hung up

The standard standing position will be as follows: (1) symmetrical on the A1–A5 axis and subjects close to each other, and (2) medial border of the feet will be 10 cm apart, and the highest point of the bilateral arch will be located on the A3–A5 axis. The static balance test has six observation indices: (1) displacement difference of the *x* and *y* axes; (2) SD of forward and backward, left and right directions; (3) average motion speed before and after, left and right; (4) motion length; (5) Central of pressure (COP) area; and (6) area ratio and length ratio under the test of the motion area and Romberg test.

Dynamic balance testing will be carried out as follows [27]. The two feet standing apart with inclined plates, entry of general data of patients, selection and evaluation module, and adjustment of the resistance buffer system as recommended by the “8” (a total of 10 files, if the file number is high the more resistance, set to “8”). The tester will be required to wear a chest position sensor, which will be located around the two nipples and connected to the midpoint of the sternum. The dynamic balance test has four observational indices: (1) Trunk Stability Index, front and rear, left and right, circumference; (2) average trajectory error; (3) test execution time; and (4) average weight force difference (in kg).

The thickness of the diaphragm will be measured by ultrasound (Tdi). Subjects will be in the supine position and breathe autonomously. It is worth noting that in order to avoid measurement error, we uniformly selected the right side of patients for measurement. All phrenic ultrasound examinations in this study are performed by the same doctor with formal ultrasound training. Therefore, a linear high-frequency probe will be positioned on the right axillary front and the probe set perpendicular to the chest wall between ribs 8 and 9. If the diaphragm is not visible in this position, the probe may be moved up to the seventh and eighth intercostals. The image of the phrenic junction consists of three layers of connective tissue, namely the bilateral hyperechoic area (pleura, peritoneum) and the intermediate mixed-type echo area (composed of the anechoic diaphragm tissue and its internal hyperechoic fascia). The three layers are parallel during respiration. A moving cursor will be used to measure the thickness of the diaphragm at the end of quiet breathing (functional residual air position; TdiFRC) and the thickness of the diaphragm at the end of maximum inspiration (forced lung capacity; TdiFVC), respectively. The values of three respiratory cycles will be measured and averaged. The change of diaphragm thickness from the end of quiet exhalation to the end of maximum inspiration will be calculated as follows: TF = (TdiFVC − TdiFRC)/TdiFRC [28].

For ultrasound measurement of phrenic muscle mobility, the degree of diaphragm mobility will be measured as the displacement distance of the diaphragm dome FRC and TLC, with subjects lying at a 45-degree angle. A convex transducer (3.5 MHz) will be placed in the medial line of the right axilla at the costal margin of the thorax, and the fixed finger will be positioned toward the skull. For each image of the M-mode record, we will determine the vertical distance between the point corresponding to the starting maximum inspiration and the point corresponding to the maximum diaphragm displacement [29].

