#### Intervention

The LQG (study group) or core stability training (control group) followed by conventional rehabilitation training (30 min each) will be completed in 2 weeks, five times in a quiet 10-m^2^ room with a background noise level ≤ 30 dB. Experienced physiotherapists will be responsible for completing the training and ensuring that the training process is conducted strictly in accordance with the research program. First, the patients should adjust to a sitting and independent standing position. Then, they should breathe smoothly through their nose, complete the upper body movements, and slowly exhale through the mouth. Meanwhile, it is worth noting that this study will not cause any side effects to patients, not negative effects, but in the process of the study, if a patient’s condition worsens, the damage caused by treatment or evaluation shall be borne by national health insurance. All patients will receive comprehensive rehabilitation provided by physiotherapists in the Shanghai Xuhui Central Hospital Department of Rehabilitation Medicine, including exercise therapy, occupational therapy, activities of daily living training, and traditional physical therapy. The intensity and frequency of comprehensive rehabilitation programs received by the two groups of patients will be the same.

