Our training is a one-to-one intervention delivered by the therapist. Before training, for the elderly, we will tell each patient that the emphasis will be on breathing and pronunciation. In order that the patient should learn correct pronunciation and breathe accurately, the patient will need to learn gradually to “feel” the key points of strength rather than the absolute power of pronunciation. For example, the patient may complete the training in a sitting or standing position. Stroke patients should learn to use healthy upper limbs to assist upper limb movement. Alternatively, the physiotherapist can stand on the patient’s side to assist in the completion of the movement and maintain the normal position of the chest, spine, and pelvis to provide a stable mechanical structure. Our training is not in the form of group exercises, but in the form of one-to-one therapist intervention.

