#### LQG action points

Stroke patients with postural dysplasia often show different degrees of hemiplegia and postural abnormalities, resulting in the loss of their ability to sit or stand. It is impossible for these patients to complete the LiuZiJue key independently and precisely without assistance. Therefore, the therapist will properly guide the completion of the movement and adjust the training position according to the patient’s functional state. As the improvement of patient’s balance ability increases, the training position will gradually transition from the sitting position to an independent standing position. As the patient’s limb function improves, the therapist will gradually reduce the amount of assistance. Both active and auxiliary limb movements are based on bilateral limb opposition. The most important goal is to complete an accurate respiratory guidance program.

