### Statistical analysis

In this study, the main indicators were determined according to the change levels of TIS before and after treatment, which were divided into three levels of CR, PR, and NR and expressed by rate or percentage. The chi-square test will be used to compare differences in efficacy between groups. The overall curative effect evaluation and the curative effect evaluation method will be employed. The calculation formula is as follows: Effective = (excellent + effective)/total cases × 100%. Secondary indicators (e.g., MPT, MBI, BBS, FMA, diaphragm thickness and mobility, static and dynamic balance ability) are all continuous data. A paired sample *t* test is often used for intragroup comparison, whereas an independent sample *t* test is often used for intergroup comparison of the difference between the two groups after treatment, and a two-sided test will be used with the significance level set at *P* ≤ 0.05. To eliminate the influence of rehabilitation intervention time, stroke type, age, and gender on the efficacy and relative size of intervention methods will be considered and the statistical method of stepwise logistic regression model adopted.

The intention-to-treat (ITT) group is divided into final analysis set (FAS) and per protocol (PP), where FAS refers to the data set obtained after minimal and fair removal of data from all randomized subjects. PP is sometimes referred to as “valid case” and “valid sample” and is a subset of the total analysis set. The subjects had sufficient adherence to the protocol to be able to estimate the effect of the treatment.

The PP population will include random patients in the ITT group but will exclude patients who do not meet the inclusion or exclusion criteria and randomly assigned patients who do not receive the actual treatment [33].

If the statistical results are the same, ITT and PP are reliable indicators. ITT results will be used if statistical evaluations are different between the two methods. As the final observation result (last observation carried forward), the missing data will be processed. The last observation value of the endpoint will be regarded as the follow-up evaluation point of missing data, and the last observation reaction will be regarded as the endpoint of the study.

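### The dynamic and standing static balance tests need a patient who can stand, but entry does not require it; if some cannot stand at baseline, the post-treatment comparison is in a group partly selected after randomisation

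*Protocol article*

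**What the plan says.** All places are in the protocol article.

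- **Test position.** Secondary outcome measurement procedures gives one set-up for the dynamic test: "The two feet standing apart with inclined plates, entry of general data of patients". No seated version is described. The static test has a seated set-up and a standing one ("The standard standing position will be as follows"). Table 2 lists each static index once, without saying which position it comes from.
- **Entry.** Inclusion criteria ask for a TIS score of 6 to 17, a level of sitting balance, a normal limb on one side or Brunnstrom stage 4 or above, and tolerance of 45 minutes of training. Standing is not mentioned. Exclusion criteria do not list inability to stand.
- **Expected ability.** LQG action points says that patients of this kind often have hemiplegia and postural abnormality "resulting in the loss of their ability to sit or stand", and that as balance improves "the training position will gradually transition from the sitting position to an independent standing position". Study group says "the patient may complete the training in a sitting or standing position". Intervention reads differently: "the patients should adjust to a sitting and independent standing position".
- **Analysis.** Statistical analysis treats static and dynamic balance as continuous. It plans paired t tests within groups, an independent-samples t test for the "intergroup comparison of the difference between the two groups after treatment", and last observation carried forward for missing data.

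**The concern.** Put together, these rules make having a dynamic balance value at week 2 depend on being able to stand at week 2. A patient who cannot stand at baseline has no earlier value to carry forward. That patient is absent from the comparison if still unable to stand, and present if standing has been gained.

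Regaining standing is something the training works towards, so the set of patients compared can differ between arms because of treatment. The arm that gets more weak patients onto their feet would add its poorest performers to its own mean and look worse on trunk stability, trajectory error and sway. The paired within-group tests would describe a different set, those with values at both times. A reader of the results would take both as comparisons of the randomised patients.

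**Working it through.** **The plan's own figure.** The sample size rests on TIS effective rates of 80% v 50%, two-sided α = 0.05 and power 0.97. With pooled variance and no continuity correction:

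n per group = [1.960·√(2·0.65·0.35) + 1.881·√(0.8·0.2 + 0.5·0.5)]² / 0.30² = (1.322 + 1.204)² / 0.09 ≈ 70.9, so 71, or 142 in total.

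The stated 142 reproduces. The 160 follows from 71 × 1.12 = 79.5, rounded up to 80 per group. Neither depends on the balance tests.

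**Who contributes a dynamic balance value under the stated rules.**

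| Baseline | Week 2 | Post-treatment t test | Paired test |
|---|---|---|---|
| Can stand | Can stand | Included | Included |
| Can stand | Cannot | Baseline value carried forward | Included, as no change |
| Cannot | Can stand | Included | Not included |
| Cannot | Cannot | Not included | Not included |

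The third row is the problem: its membership is decided after randomisation.

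**Size, on assumptions.** The documents give no share unable to stand and no rate of gaining it. Let *s* be the share unable at baseline, *a* and *b* the shares of those who can stand by week 2 under LQG and control, and *d* how much worse new standers score, in SD. With no true difference among the other patients:

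bias = d·[ s·a/(1 − s + s·a) − s·b/(1 − s + s·b) ], against LQG when a > b.

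For s = 0.40, a = 0.25, b = 0.10, d = 1: 0.10/0.70 − 0.04/0.64 = 0.143 − 0.0625 = 0.080 SD.

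| s | a v b | Testable at week 2, LQG v control | Bias, d = 0.5 | Bias, d = 1 |
|---|---|---|---|---|
| 20% | 25% v 10% | 85% v 82% | 0.017 SD | 0.034 SD |
| 20% | 40% v 20% | 88% v 84% | 0.022 SD | 0.043 SD |
| 40% | 25% v 10% | 70% v 64% | 0.040 SD | 0.080 SD |
| 40% | 40% v 20% | 76% v 68% | 0.046 SD | 0.093 SD |

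The bias is about 0.02–0.09 SD, and 12–36% of an arm has no value.

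**Against sampling error.** In the 70% v 64% case, 80 × 0.70 = 56 and 80 × 0.64 ≈ 51 patients are measured. The standard error is √(1/56 + 1/51) ≈ 0.19 SD, so 0.080 SD is about 0.4 standard errors. That moves a two-sided 5% error rate to about 7%.

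**A different assumed model.** Suppose week-2 balance is normal with SD 1, LQG shifts it by 0.5 SD, and it is measured only above a standing threshold. The mean among those measured is μ + φ(c − μ)/[1 − Φ(c − μ)]. If 95%, 80%, 60% or 50% of controls can stand, the difference seen is 0.43, 0.33, 0.24 or 0.21 SD. The direction is the same and the loss larger, but both the 0.5 SD shift and the sharp threshold are assumptions.

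**The case against.** The strongest reply is that nothing shows patients unable to stand are enrolled in number.

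- The sentence in LQG action points on losing the ability to sit or stand describes stroke patients with postural problems in general. Since entry requires sitting balance, it is not a description of the sample. The wheelchair class in the Berg Balance Scale key is likewise a generic scale category.
- A patient who trains seated may still be able to stand for a test.
- Intervention speaks of independent standing, and routine rehabilitation in Control group includes walking between parallel bars. The limb-function and endurance criteria make entry stricter than sitting balance alone.

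All of this stands and makes the point conditional. It does not remove it: no criterion secures standing, and the training sections do foresee progress from sitting to independent standing.

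A second reply concerns the t test. The plan's wording ("an independent sample *t* test is often used for intergroup comparison of the difference between the two groups after treatment") reads most naturally as post-treatment values, but change scores are possible. New standers have no baseline and would drop out of a change score, and the bias described here would go. That also stands, and is a reason to say which is meant.

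A third reply is that scoring of untestable patients belongs in an analysis plan that is not shown. That would be fair if the article were silent. Here it fixes the test position, the entry rules, the t test and the carry-forward rule, and it is following these together that yields the non-randomised comparison.

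A reader might infer that the balance results are certain to be biased, or that half of a real benefit would be lost. The documents support neither: the first needs a share unable to stand that is not given, and the second comes from a model whose inputs are all assumed.

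**Conclusion.** The concern holds in conditional form. If some enrolled patients cannot stand at baseline, the post-treatment comparison of the dynamic and standing static measures is not a comparison of the randomised groups, and last observation carried forward does not repair it.

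The size is uncertain and probably modest: about 0.02–0.09 SD against the arm that gets more patients standing, if 20–40% cannot stand at baseline, 25% v 10% or 40% v 20% of them gain it, and new standers score 0.5–1 SD worse. If nearly everyone can stand, almost nothing remains; under the threshold model the loss is larger. The figures also assume that post-treatment values, not changes, are compared.

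Only secondary outcomes are touched. The seated static test, the primary TIS outcome and the sample size are not affected. The change is worth making because it is cheap and because baseline ability to stand must be recorded before randomisation to be usable.

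**What to change.** In Secondary outcome measurement procedures (with Table 2) and Statistical analysis:

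1. State which static indices are taken seated and which standing.
2. Record, before randomisation, whether each patient can do the standing tests.
3. Restrict the between-group comparison of the standing static and dynamic measures to patients able to do them at baseline, and state whether it uses post-treatment values or changes.
4. Report by arm, in all randomised patients, the number able to do the test at week 2.
5. Add a sensitivity analysis that ranks patients unable at week 2 as worst. This is one of several reasonable ways to count them and need not replace the t test.

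Secondary outcome measurement procedures, Inclusion criteria, Intervention, Study group and LQG action points must also be reconciled on test position, training position and entry criteria. Which of them should give way is for the investigators.

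The seated static test should not simply be declared feasible for everyone: its described posture has crossed arms and raised shoulders, while entry allows only one side with normal limb function.

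**Cost.** One extra baseline item, a smaller analysed set for the standing measures and a little extra analysis. No new test is needed.

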### Adverse event collection procedure during the trial

Adverse events and procedures during the trial will be reported, processed, and recorded in a timely manner. This study will complete a 2-week clinical intervention to identify the reasons for adverse events and to ensure that patient safety, health, and rights are maintained. Serious adverse events will be submitted to the principal investigator within 24 h. The clinical trial office and ethics committee of Shanghai Xuhui District Central Hospital will jointly put forward reasonable suggestions.

### Trial setting

The rehabilitation department of Shanghai Xuhui District Central Hospital will carry out this study. Physical therapists will provide comprehensive rehabilitation for all patients, including exercise therapy, occupational therapy, speech therapy, and traditional rehabilitation.

### Inclusion criteria

The following will be criteria for inclusion of subjects in the study:
Meet the diagnostic criteria of cerebral infraction or cerebral hemorrhageMeet traditional Chinese medicine (TCM) diagnostic criteria of strokeFirst onset of stroke, with trunk postural control disorderTIS evaluation score between 6 and 17 and a sitting balance greater than two levelsBetween 40 and 80 years oldCourse of disease 2 weeks to 6 monthsGood physical strength; can withstand 45 min of trainingAt least one side movement function of a normal limb or Brunnstrom stage ≥ 4Stable vital signsAgree to sign informed consent document

### Exclusion criteria

The following will be exclusion criteria for potential subjects in this study:
Consciousness disorder, severe cognitive dysfunction, and hemianopiaConcomitant dysarthria or aphasiaPhysical training cannot be tolerated for 45 minHeart, brain, kidney, and other organs with acute diseaseSerious mental disordersModified Mini Mental State Examination score ≤ 23

### Study population and recruitment

The study will recruit 160 patients aged 40–80 years who have been diagnosed with cerebral apoplexy in the rehabilitation department of Xuhui District Central Hospital in Shanghai from March 2018 to March 2021. First, before the start of the study, doctors in the inpatient department of rehabilitation medicine should be informed of the criteria of potential study patients who need to be included in the study, as well as the purpose of the study, and then they should be referred to the researchers of the study. Second, the principal investigator will briefly introduce the inclusion and exclusion criteria for this study and provide the researchers with possible inclusion information, as well as the potential risks and advantages. Third, If patient is interested in the study, the primary researchers will further provide more detailed information and answer any questions raised. If the patient agrees to participate in the study, the patient or the patient’s family members will sign the informed consent to guarantee the patient’s privacy. Finally, after the patients and their families have signed the informed consent form, the main researchers will include subjects who meet the requirements according to the TIS.

#### Blinding

Patients will be randomly assigned through random coding generated by the IBM SPSS Statistics software to ensure that the evaluator is blinded. Only the major researchers will know the order of the random assignments. Outcome assessors will be blinded; that is, the outcome assessors and care providers will be different doctors. The outcome assessors and care providers shall not exchange information in the implementation of the experiments, and the outcome assessors shall not ask the subject for the intervention. In this study, only the assessors will be blinded, so the study does not involve unblinding.

#### Intervention

The LQG (study group) or core stability training (control group) followed by conventional rehabilitation training (30 min each) will be completed in 2 weeks, five times in a quiet 10-m^2^ room with a background noise level ≤ 30 dB. Experienced physiotherapists will be responsible for completing the training and ensuring that the training process is conducted strictly in accordance with the research program. First, the patients should adjust to a sitting and independent standing position. Then, they should breathe smoothly through their nose, complete the upper body movements, and slowly exhale through the mouth. Meanwhile, it is worth noting that this study will not cause any side effects to patients, not negative effects, but in the process of the study, if a patient’s condition worsens, the damage caused by treatment or evaluation shall be borne by national health insurance. All patients will receive comprehensive rehabilitation provided by physiotherapists in the Shanghai Xuhui Central Hospital Department of Rehabilitation Medicine, including exercise therapy, occupational therapy, activities of daily living training, and traditional physical therapy. The intensity and frequency of comprehensive rehabilitation programs received by the two groups of patients will be the same.

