**Methods/design:**

This study is a single-center randomized controlled trial in which 160 stroke patients are randomly divided into a study group and a control group. Patients in the study group will receive LQG combined with conventional rehabilitation therapy, and patients in the control group will receive traditional core stability training combined with conventional rehabilitation therapy. All treatments will be done for 45 min/day, five times per week, for 2 weeks. The primary outcome (Trunk Impairment Scale) and secondary outcomes (Berg Balance Scale, Fugl-Meyer Assessment, Modified Barthel Index, Maximum Phonation Time, Dynamic and Static balance testing, and thickness and the mobile degrees of diaphragm) will be measured at baseline, 2 weeks, and the end of the rehabilitation course.

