#### Control group

Patients in the control group will receive traditional core stability training and conventional rehabilitation therapies. Routine rehabilitation training will include drafting training, passive joint movement, walking between parallel bars, and occupational therapy, among others. At the same time, core stability training will include abdominal training in the supine position, double-bridge movements, single-bridge movements, balance ball half-bridge movements, and forward and backward movement of the sitting pelvis. The patient will be sat on a Bobath ball and use the Bobath handshake to control the flexion, extension, lateral flexion, and rotation of the torso. Before the training begins, the therapist will inform the patient of the brief action instructions. For patients with poor respiratory control, manipulation will be adopted to stimulate their abdominal muscle group contraction, and necessary manipulation should be undertaken according to the different limb functions of the patients. The duration of conventional rehabilitation training will be five times per week, 30 min per session, lasting for 2 weeks. The traditional core stability training will last for 15 min, five times per week, for 2 weeks. All of the control group interventions for traditional core stabilization training will be performed separately by three experienced therapists.

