#### Study group

In addition to receiving conventional rehabilitation training, patients in the study group will be required to complete the LQG treatment. Patients allocated to the study group will be engaged in LQG rehabilitation programs in addition to conventional rehabilitation therapies. The sequence will be routine rehabilitation and then core stability training. Each time, the rehabilitation course will be divided into LQG for 15 min and normal rehabilitation training for 30 min. The study group will complete training five times per week for 2 weeks in a quiet room. For traditional core stabilization training, all study group interventions will be performed separately by three experienced therapists.

The key points of LQG oral guidance will consist of pronunciation and breathing. For “xu,” pronunciation will be assisted by the teeth. Space will be left between the teeth and the tongue, with the upper and lower teeth parallel. Air will be drawn from the space between the teeth, as well as between the teeth and the tongue, and the corners of the mouth will be pulled back a little. When exhaling and pronouncing, the “he” will be pronounced with the aid of the tongue. The upper teeth will be tapped with the sides of the tongue and air exhaled between the tongue and the upper jaw. During the exhalation and pronunciation, the “hu” sound will be assisted by the throat. The sides of the tongue will be bent upward and the lips forward, forming a circular opening through which the patient will exhale. During exhalation and pronunciation, the “si” will be pronounced with the assistance of the teeth. There will be a narrow gap between the upper and lower teeth. The patients will lightly touch their lower teeth with the tip of their tongue and exhale air between their teeth. During the exhalation and pronunciation, the “chui” will be pronounced with the assistance of the lips. The tongue and the corner of the mouth will be pulled back, as will the lips into the stretched position, making the back teeth parallel and thus exhaling air from the throat between the sides of the tongue and the stretched lips. In the exhalation process, the “xi” will be pronounced with the assistance of the teeth. The lower teeth will touch the tip of the tongue, and the corners of the mouth will be slightly tilted back, the posterior teeth gently closed, and air exhaled through the space between the posterior teeth [30–32].

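### The treatment sections conflict on the order of the two components and the number of sessions, and the Study group section twice names the control treatment as part of the study arm

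*Protocol article*

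**What the plan says.** Four places in the protocol article describe what is delivered.

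- **Abstract, Methods/design:** "All treatments will be done for 45 min/day, five times per week, for 2 weeks".
- **Intervention:** LQG for the study group or core stability training for the control group, "followed by conventional rehabilitation training (30 min each) will be completed in 2 weeks, five times".
- **Control group:** "The duration of conventional rehabilitation training will be five times per week, 30 min per session, lasting for 2 weeks", and "The traditional core stability training will last for 15 min, five times per week, for 2 weeks".
- **Study group:** "the rehabilitation course will be divided into LQG for 15 min and normal rehabilitation training for 30 min", and "The study group will complete training five times per week for 2 weeks in a quiet room". The same section says "The sequence will be routine rehabilitation and then core stability training" and later "For traditional core stabilization training, all study group interventions will be performed separately by three experienced therapists".

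The abstract and the Trial design section name the comparison: LQG plus conventional rehabilitation in the study group, core stability training plus conventional rehabilitation in the control group. The Statistical analysis section makes membership of the per-protocol set depend on sufficient adherence to the protocol, and excludes patients who were ineligible or did not receive their actual treatment.

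**The concern.** The Intervention, Control group and Study group sections are the ones a therapist would work from. The Intervention section asks that training keep strictly to the research program, but on the order of the components and the number of sessions the text gives two answers.

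The wording on study-arm content matters most for the comparison. The trial sets LQG against core stability training. If some study patients were given core stability training as well as LQG, the comparison for them would become LQG plus core training against core training, which is a different question. No analysis could undo that once treatment had been delivered.

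A lesser consequence concerns the per-protocol set. A patient treated as one section describes could count as departing from another, so adherence has no single standard.

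**Working it through.** The plan's own figure comes first, then each point is set side by side.

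**Session length and total time.** The Control group and Study group sections each give 15 min of the trial component and 30 min of conventional rehabilitation.

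- Session: 15 + 30 = 45 min, which reproduces the abstract's daily figure.
- Sessions: 5 per week × 2 weeks = 10.
- Total: 45 × 10 = 450 min, of which 15 × 10 = 150 min is LQG or core training.

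The 30-minute parenthesis in the Intervention section can be read in two ways.

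- It covers each conventional session only. It then agrees with the Control group and Study group sections, and there is no conflict on length.
- It covers each of the two components. A session is then 30 + 30 = 60 min, against 45 min elsewhere.

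The sentence does not settle which is meant, so length is an ambiguity and not a proven contradiction.

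**Number of sessions.**

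| Section | Wording in substance | Sessions |
|---|---|---|
| Abstract, Methods/design | five a week, two weeks | 5 × 2 = 10 |
| Control group | five a week, two weeks | 5 × 2 = 10 |
| Study group | five a week, two weeks | 5 × 2 = 10 |
| Intervention | five times in two weeks | 5 |

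This conflict does not depend on how the 30 minutes are read.

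**Order.**

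| Section | First | Second |
|---|---|---|
| Intervention (both arms) | LQG or core training | conventional rehabilitation |
| Study group | routine rehabilitation | core stability training |

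For the study arm, the two orders are opposite.

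**Content of the study arm.**

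| Section | Study arm receives |
|---|---|
| Abstract; Trial design | LQG + conventional rehabilitation |
| Intervention | LQG, then conventional rehabilitation |
| Study group, opening sentences and time split | LQG + conventional rehabilitation |
| Study group, sequence sentence | routine rehabilitation, then core stability training |
| Study group, delivery sentence | interventions placed under traditional core stabilization training |

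The Study group section's own time split can be checked against the abstract's 45 min: 45 − 15 (LQG) − 30 (conventional) = 0 min left for core stability training. Its two sentences naming core training therefore disagree with its own time split as well as with the other sections.

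**The case against.** The strongest reply is that these are drafting faults around a design that is otherwise clear. Most of that stands.

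- **A reader might infer that the tested contrast is not fixed.** The documents do not support that. The abstract and the Trial design section state the contrast consistently, the Intervention section labels the two arms in the same way, and the Study group section opens by giving the study arm LQG in addition to conventional rehabilitation. Its time split leaves no slot for core training, and its delivery sentence closely mirrors the last sentence of the Control group section, so a copying slip is a likely explanation.
- **A reader might infer a definite conflict on session length.** The conventional-only reading removes it, and the 45-minute tolerance in the inclusion and exclusion criteria fits that reading.
- **A reader might be tempted to quote a wide range of total therapy time.** A total of 600 min (60 × 10) takes session length from one reading of the Intervention section and session count from sections that give 15 + 30 min. A total of 225 min (45 × 5) mixes sections in the opposite way. No single section states either figure, so no such range is claimed here.
- **A reader might infer that the arms are planned to receive different amounts of therapy, or that per-protocol status cannot be judged at all.** Each schedule in the text applies equally to both arms. The explicit per-protocol exclusions are ineligibility and not receiving the actual treatment, not minutes or order. The plan also relies on the ITT result if the two analyses disagree.

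The reply does not remove the opposite orders, the 5 against 10 sessions, or the two sentences that name the control treatment in the study arm. That three places agree on the count makes an omission in the fourth plausible, but it does not correct the text.

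**Conclusion.** The point holds as an inconsistency in the operative treatment text, not as a flaw in the design. Three conflicts are established: the order of components in the study arm, 5 against 10 sessions on a literal reading of the Intervention section, and two statements in the Study group section that name the control treatment. Session length, 45 or 60 min, is ambiguous rather than contradictory.

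The effect on the result cannot be sized from the document, because it depends on which text the therapists follow. If all of them follow one schedule and deliver LQG without core training in the study arm, the comparison is unaffected. If some follow the sequence sentence and add core training, the contrast for their patients changes. The sample size calculation is not touched. Which schedule, order or content is right is a clinical matter and is not judged here.

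**What to change.** Reconcile the abstract, Intervention, Control group and Study group sections so that both arms have one stated session length, number of sessions and order of components. Make clear what the 30-minute figure in the Intervention section refers to. State plainly in the Study group section whether study patients receive any core stability training, and correct the sequence and delivery sentences to match. The clinical team decides the content. Then state that adherence for the per-protocol set is judged against the reconciled text.

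The cost is a correction of protocol wording and a note to the treating therapists. Recruitment began on 1 March 2018, so the team should also confirm from treatment records which version has been delivered so far.
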